# Individual Placement and Support for persons with alcohol and drug addiction in a Swedish context (IPS-ADAS): study protocol for a randomised controlled trial

**DOI:** 10.1186/s13063-024-08007-x

**Published:** 2024-03-27

**Keywords:** Supported employment, Recovery, Mental health, Addiction services, Homelessness, Proactive aging

## Abstract

**Background:**

Employment is a vital source for experiencing well-being and lowering the risk of long-term social marginalisation and poverty. For persons with alcohol and drug addiction, it may also improve sobriety. However, the unemployment situation for this group reflects the knowledge gap in effective interventions to support employment. While Individual Placement and Support (IPS) is recognised as evidence-based supported employment for those with serious mental health problems, no scientific evidence for the target group of addiction exists to date. The aim of the present IPS for Alcohol and Drug Addiction in Sweden (IPS-ADAS) trial is to study whether IPS has an effect on gaining employment for this group.

**Methods:**

The IPS-ADAS trial is a multisite, pragmatic, parallel, and single-blinded, superiority randomised controlled trial (RCT). Participants (*N* = 330) will be randomly assigned (1:1) and participate in IPS plus treatment as usual within Addiction Services (IPS + TAU) or Traditional Vocational Rehabilitation (TVR) available plus TAU (TVR + TAU) for 12 months. The principle of intention-to-treat (ITT) will be applied. The hypothesis is that a significantly larger proportion of IPS + TAU participants will be employed for > 1 day (primary outcome), reach employment sooner, work more hours and longer periods of time, and have a higher income as compared to TVR + TAU participants at 18-month follow-up. We further anticipate that those who benefit from IPS + TAU will use less alcohol and drugs, experience better health, and use less care and support, including support from the justice system, in comparison to TVR + TAU participants, at 6, 12, and 18 months. A supplementary process evaluation, using the IPS Fidelity Scale (25 items) and adhered interviews will address delivery and receipt of the IPS as well as contextual hinders and barriers for coproduction and implementation. Working age (18–65), willingness to work, unemployment, participation in an information meeting about the RCT, treatment for addiction diagnosis, and being financially supported by welfare, constitute eligible criteria.

**Discussion:**

A primary study on the effectiveness of IPS on employment for the new target group of addictions will add to the international IPS knowledge base and inform national policy to include the underrepresented group in working life.

**Trial registration:**

WHO International Clinical Trials Registry Platform ISRCTN10492363. Registered on 14 August 2023.

**Supplementary Information:**

The online version contains supplementary material available at 10.1186/s13063-024-08007-x.

## Background

Alcohol and drug addiction severely contribute to the disease burden (e.g. cardiovascular, sepsis, cancer, suicide, depression, anxiety), and worsen the social and economic situation (e.g. unemployment, homelessness, incarceration, child neglect) [1–3]. In Sweden, there is an inverse relationship between increased use of care and younger age (18-34), and mixed abuse is highest in this group [4]. The young risk long-term social marginalisation, poverty, sickness, and premature death [2, 5]. Hence, addiction severely impacts people’s lives and unemployment is highly prevalent, both nationally and internationally, and the cost of unemployment and sick-leave benefits and the burden for care, school, treatment, and homelessness incentives is huge. The unemployment situation for this group further reflects the knowledge and practice gap of effective interventions to support employment within Addiction Services (AS), internationally [6] and in Sweden [4, 7, 8]. Employment is not being considered a goal in long-term treatment and rehabilitation [9]. If nothing is done, the interrelation between addiction and unemployment continues to foster a downward spiral, since ongoing usage may decrease opportunities to reach and keep employment, and unemployment is likely to increase the use of alcohol and drugs. Effective interventions that both prevent and reduce abuse are critical to develop, study, and implement [1, 10, 11].

Employment has been described as an indispensable tool for transition into recovery for employed individuals in AS treatment [9]. A review further suggests employment as an outcome measure of treatment, but also as a critical ingredient in future innovations within ASs [12]. Employment forms part of society and has shown to be a vital source for experiencing meaningfulness, having economic resources, participating in society, and developing identities [9, 13, 14] and for lowering the risk of long-term social marginalisation and poverty. Work may also improve sobriety, health and well-being and thus support proactive ageing [15]. While the Supported Employment intervention of Individual Placement and Support (IPS) holds a promise [16] and is already recognised in the national policy for AS in Sweden [17], it is yet only an evidence-based intervention for those with serious [18] and moderate mental health problems [18–20]. There is also evidence to suggest that IPS improve health, quality of life, and well-being among those with mental health problems [21–27]. However, no scientific evidence for persons with alcohol and drug addiction exists to date [28, 29], with the exception for a pilot waitlist study [30] and analyses of pooled original data [31], indicating an effect of IPS on employment for the target group.

Previous research shows that context matters and impacts on IPS implementation and thus employment outcomes [16, 32]. Implementation research shows that the primary focus of the Swedish welfare system is on the objective, on organisational constituents rather than on the subjective and experience-based knowledge of users [33–38]. Government-controlled welfare organisations regulate and foster a stepwise rehabilitation chain of fragmented services which is incompatible with the cohesive, integrated, and person-centred approach of IPS. Thus, the uptake may be slow and implementation barriers are critical to assess [16, 25, 33]. Timely, however, a recent national policy for AS addresses the urgency to overcome organisational boundaries to support user goals, a policy that works in favour of the integrated approach of IPS [15].

We acknowledge that the implementation of IPS poses challenges to mindsets and behaviours among professionals within the new field with a tradition of focusing on diagnoses, treatment, disabilities, and at best, stepwise rehabilitation services. We further acknowledge that a trial of complex interventions may be challenging to design, pursue and complete in practice, which may lead to over- and underreported results [39, 40]. Research questions, interventions, and outcomes need to be necessary to the public [41], and interventions more fully described and implemented in practice. To meet this challenge, we suggest coproducing the implementation of IPS and the IPS-ADAS trial within this entirely new field of practice. In the UK, coproduction has long been a policy to mobilise knowledge and innovations in the NHS [42]. It refers to that services need to be built on a knowledge framework where those who receive and deliver them are involved [43–45], which also applies to trial research [46]. Such democratic research may close the gap between the production of knowledge and the actual use of it [47]. A knowledge framework of researchers, professionals, and service users to enhance the implementation and progression of the trial is therefore advocated. Clarity of how coproduction may be evaluated and what level of involvement may be acceptable in a trial context is however lacking but critical to explore [48, 49]. While we want to develop a scientific basis for IPS for the target group, we also want to inform how a sustainable IPS practice in a new field of AS may be built.

## Objectives

The aim of the IPS-ADAS trial is to add to the development of a scientific basis for IPS for the target group of persons with alcohol and drug addiction, with the possibility to influence policy and inform the implementation of an IPS practice in a new field in a Swedish welfare context.

The hypothesis is that a significantly larger proportion of IPS plus treatment as usual (IPS + TAU) participants will be employed for > 1 day at 18-month follow-up (primary outcome), reach employment sooner, work more hours and longer periods of time, and have higher income as compared to traditional vocational rehabilitation (TVR) intervention plus TAU (TVR + TAU) participants among 330 participants. We also anticipate that those who benefit from IPS + TAU will use less alcohol and drugs, experience better health, quality of life and well-being, and use less care and support in comparison to TVR + TAU participants, at 18-month follow-up. A process evaluation, using the Medical Council Framework (MRC) [39] and IPS Fidelity Scale (25 items) [50] and adhered interviews will help to describe the delivery and receipt of the IPS as well as contextual hinders and barriers for coproduction and implementation.

The research questions are:Is IPS + TAU significantly more effective than TVR + TAU at 18-month follow-up in terms of employment (primary outcome), other vocational outcomes, addiction, and care use (secondary outcomes)Is IPS + TAU significantly more effective than TVR + TAU at 18-month follow-up in terms of health, quality of life, and well-being (secondary outcomes)?How and which decisions and processes may be coproduced, what are the benefits and challenges of coproduction, and what mechanisms of coproduction may impact on progress of the trial and the implementation of IPS in a new field?

## Methods

### Trial design

This study protocol presents the IPS-ADAS trial, a multisite, pragmatic, two-arm parallel single-blinded, superiority randomised controlled trial (RCT) of 18 months. Participants (*N* = 330) will by randomly assigned (1:1) and participate in IPS + TAU or TVR + TAU interventions in a Swedish context for 12 months (Table 1). Principle of intention-to-treat (ITT) will be applied and the protocol follows the standards of the 2013 statement of Standard Protocol Items: Recommendations for International Trials (SPIRIT) [51] while the design follows the criteria of randomised controlled of non-pharmacological treatment, the Consolidated Standards of Reporting Trials (CONSORT) [52]. The trial register number is ISRCTN10492363.

**Table 1 Tab1:**
[figure not shown]
Schedule of enrolment, interventions, and assessment (SPIRIT figure)

*TAU* standard addiction treatment as usual, *IPS* Individual Placement and Support, *TVR* Traditional Vocational Rehabilitation, *ES* Empowerment Scale, *POES* Profiles of Occupational Engagement Scale, *HADS* Hospital Anxiety and Depression scale, *EuropASI-E* E-section of European Addiction Severity Index, *EQ-5D-5L* EuroQoL 5L—health-related quality of life, M*ANSA* Manchester Short Assessment of Quality of Life, *WHO-5* Well-being Scale

### Study setting

The research will be conducted at the Department of Health Sciences at Lund University and involve the Department of Psychiatry, Habilitation and Aids of County Council of Region Skåne. The national research network of the Centre for Evidence-based Psychosocial Interventions (CEPI, www.cepi.lu.se), the international Inter-University Consortium (IUR, www.du.edu/iur), and the user organisation of Verdandi (www.verdandi.se) will be further engaged. Three Addiction Services sites (Lund/Malmö, Stockholm and Södertälje; Municipalities and/or County Council) are included to promote geographical diversity (middle and south of Sweden) as well as locations with various proportions of citizens with foreign backgrounds (Lund 28.6%; Malmö, 46.7%; Stockholm, 34.4%; Södertälje, 57.7%) [4].

### Eligibility criteria and informed consent

Eligibility criteria concern having a working age of 18–65, willingness to work, being unemployed, participation in an IPS-ADAS trial information meeting, being diagnosed with addiction disorder (i.e. alcohol and/or drugs) as a primary diagnosis and in treatment at outpatient AS within the healthcare Region and/or related Municipality, and being financially supported by welfare system (i.e. the Municipality, Public Employment Service or Social Insurance Agency).

Exclusion criteria regard having a lack of interest to become employed and to participate in the IPS-ADAS trial, ongoing abstinence treatment, disability because of another main condition (e.g. serious mental illness, somatic illness), lack of ability to fully engage in IPS due to acute homelessness, being engaged in a lengthy legal process, occupied with plans of suicide, or having had recent attempts (< 3 months).

Eligibility criteria for the sites will concern being an AS provider within the publicly financed healthcare of Region Stockholm and Region Skåne and/or City of Stockholm, Municipality of Södertälje, and Municipality of Lund/Malmö. The trial may be extended to other sites. AS in Sweden are typically divided between Regions and Municipalities and new governmental directives for coproduction and person-centeredness of services are policy [15].

The Employment Specialist is the key professional of the IPS intervention and will have formal IPS training, work experience of IPS, and a position within above stated regions or municipalities.

The AS provider will take informed consent. Initially the professional will provide verbal and written information about the IPS-ADAS trial, including the possible benefits, risks, and alternative interventions. If interested, presumptive participants will be scheduled for an obligatory IPS-ADAS information meeting in a group format or individually. A research administrator, a professional from AS, and a user representative with experienced knowledge of addiction and returning to work will aid presumptive participants to understand the trial more fully, criteria, confidentiality, and the voluntary nature of participation. If criteria are met, the informed consent form may be signed, available on request from the corresponding author.

### Interventions

The comparative intervention will consist of Traditional Vocational Rehabilitation (TVR) services plus Treatment as Usual (TVR + TAU) within AS. We consider TVR the best choice since the service concerns the standard employment support within the Swedish welfare system. The TAU elements of AS treatment regard reducing substance use, increasing health, quality of life, and wellbeing, and securing housing (1–10 h a week). Both the IPS and TVR interventions concern integrating TAU services, including usual care pathways and the use of any medication.

#### The IPS intervention

IPS is guided by an ES who provides IPS to a caseload of < 20 participants for 12 months, with the possibility to abate and refer quality support beyond this point. The time frame is referenced to previous IPS research [22, 28, 29, 53]. The ES works in coproduction with the participant and the IPS network of the AS team (TAU), family and friends (if applicable), and professionals from the Social Insurance Agency (SIA), Public Employment Service (PES), and keep frequent and quality contacts with employers. The professional role of the ES concerns good-quality emphatic counselling according to eight IPS principles (not to be understood or carried out in any particular order): (1) competitive employment as a primary goal, (2) eligibility based on participant’s choice (zero exclusion), (3) rapid job search, (4) integration of IPS with treatment, (5) job search based on personal preferences, (6) on-going support on and off worksite as needed, (7) benefit counselling (SIA/PES) in an early stage, and (8) systematic recruitment and quality engagement with local employers. The dose of delivery is individualised but involves (1) an engagement phase of sharing lived experience and expectations and building a mutual relationship (ES + user), (2) a phase of coproducing and completing a career profile and -plan based on user interest and preferences, (3) a job-seeking and -development phase and if employment is gained, (4) a supported employment phase in which mobilised support strategies of IPS are intertwined. Notably, within the process of IPS support, education efforts are also supported and integrated with the career goal of gaining employment [54–56]. Phases 1 and 2 last for about 1 month, phase 3 until employment is reached, and phase 4 the remaining time. Against the backdrop of previous IPS research [22], the dosage of phases 1, 2, and 3 is approximately 1 h a week, while phase 4 requires 20 min per week. In the Swedish National Guidelines for care and support in cases of substance abuse and addiction, IPS is prioritised as 3 on a 10-point scale, where 1 represents the highest priority [17].

#### The control group intervention

The TVR + TAU intervention will be delivered by professionals within AS and the Municipalities but also from professionals from the Public Employment Service (PES) and the Social Insurance Agency (SIA) throughout the 12-month intervention period. TVR is facilitated through pre-assessment work ability stages according to the institutional logic and regulation of each organisation involved and in connection to regulations of social, sick-leave, and unemployment benefits. In case of sobriety, the first phase 1) involves pre-vocational rehabilitation, including Supported Employment strategies, within labour market units at the municipality (1–5 h per week). If the ability to work across the entire labour market is met, participants may move on to phase 4. If not, users may enter 2 pre-vocational training in day centres (municipality) for engagement in meaningful activities, regulated by law to 5–20 h a week. Phase 3 is vocational training in internship placements (20–40 h a week) through the PES/SIA or municipality, while at the last phase 4, application for employment positions through the PES, for example, may be pursued. In the national guidelines, TVR is prioritised as 6 on a 10-point scale [17]. The TVR intervention resembles an addition to AS treatment (TAU).

### Guidance for discontinuing interventions and promotion of adherence

The criterion for discontinuing or modifying allocated interventions is when participants withdraw consent. In case of worsening symptoms or need of additional support, all participants will receive TAU in addition to IPS and TVR. Thus, IPS employment specialists who are integrated into the treatment team will be noted. Furthermore, the IPS is a person-centred service and is naturally modified in relation to the needs, preferences, and resources of the study participant. The flexible approach with one-to-one communications for imparting and sharing knowledge, scheduled according to the preferences and support needs of the participants affects adherence. IPS further entails ongoing support and outreach activities to maintain contact. Ambivalence, benefits, as well as perceived barriers, are issues discussed throughout the intervention even though study participants are not in an active phase (e.g. adjustment of medication or a dormant period). The coproduced IPS-career profile and plan content will further reinforce, motivate, and encourage participants. Adherence barriers will be addressed in biweekly IPS supervision sessions for employment specialists at each site and at project meetings. Participants in the TVR + TAU intervention will not receive any overall or single guidance, but adherence will be improved and monitored within each step of the rehabilitation process by the relevant welfare actor.

Trial adherence is facilitated by the online RedCap system, providing e-mail reminders to respond to questionnaires. Personal support, including contact and support from a peer, and pen-and-paper options will be available. Preferred contact information and response trajectories will be monitored by research assistants and communicated to the trial management group and operational work groups to enhance assistance and trial adherence of participants.

### Outcomes

Assessment of primary, secondary, and other self-reported outcomes is done at baseline (-*t*^1^), before allocation, and at 6–12–18 months (*t*^1^–*t*^3^) (Table 1). Vocational primary and secondary outcomes will be retrieved retrospectively (> 18 months), via Statistics of Sweden from the LISA register data base (Swedish Longitudinal Integrated Database for Health Insurance and Labour Market Studies) [57]. Secondary and other self-reported variables are reported in an online RedCap system [58]. Adverse Events will be collected continuously.

#### Primary outcome

The primary outcome concerns differences in proportions of gaining competitive employment between the two arms (yes/no, 1 day) at 18 months (*t*^4^), reflecting any employment registered during the trial period. The operationalisation of employment status and time frame are standard in IPS trials internationally and in Sweden [20, 22]. The primary outcome will be collected by Statistics Sweden from the LISA register and be delivered to the trial project team coded. Register data will be validated against users’ self-registration of employment status in the Addiction Severity Index (ASI), and logbooks of employment specialists, by an independent researcher. Self-employment data will also be collected.

#### Secondary outcome

Secondary vocational outcomes are time to event (employment), total time (days) in employment, job tenure (time-based), total employment, proportion of full-time work (40 h/week), and income (amount and benefit type) will be retrieved retrospectively from the LISA register. Secondary outcomes corresponding to health, quality of life, and well-being are descriptive, ordinal, or continuous.

The Empowerment Scale (ES) is chosen to detect changes in perceived empowerment for the benefit of health. It entails 28 statements reflecting five subscales: self-esteem/self-efficacy, power/powerlessness, community activism and autonomy, optimism and control over the future, and righteous anger. Each statement is scored on a 4-point scale ranging from strongly agree [1] to strongly disagree [4], with a total score range of 28–112. Higher scores represent higher levels of empowerment. The Swedish version has shown good internal consistency in previous trials [21, 23].

The Profile of Occupational Engagement Scale (POES) is used to address changes of time use patterns and behaviour as reflected by the engagement level in activities and community life. The first part involves completing a 24-h yesterday time-use diary with 1-h intervals, and a four-column solution corresponding to time, activities, social and geographical environments, and personal reflections about each performance entity. The second part helps to assess the diary content in relation to engagement dimensions according to 9 items on a 4-point scale: daily rhythm of activity and rest, variety and range of occupations, place, social environment, social interplay, interpretation, meaningful occupations, routines, and initiating performance, with a total score range of 9–36. Higher scores are consistent with greater health [59–62]. The POES has sound psychometric properties [61, 62] and has been used to detect change as a primary or secondary outcome measure in previous lifestyle interventions [63–66] and IPS trials [21, 23].

The Hospital Anxiety and Depression Scale (HADS) has 14 items and assists to measure mental health in terms of differences between intervention arms regarding anxiety (7 items) and depression (7 items) [67], also among persons with substance abuse [68]. It is rated on a 4-point scale (0–3 range), and anxiety and depression are scored separately (0 to 21). A higher score indicates a greater level of anxiety and depression, and cut-off scores are available [69]. HADS is used in general medical settings, including occupational health, with sound psychometric properties [70].

The Assessment Severity Index (ASI) is widely used to address the severity of substance use, health and social problems and the need of treatment. ASI holds 7 key domains: medical status, employment and support, drug and alcohol use, legal status, social and psychiatric status [71, 72], and has sound psychometric properties [73]. In the present IPS-ADAS trial, the ASI interview questions are replied online (RedCap), with support from the research administrator if needed. Variables relevant to sociodemographic characteristics, substance abuse and care and support are particularly of interest for the present study (i.e. age, gender/gender identity, ethnicity, civil status, diagnosis, substance use, housing situation, income, benefit type, sick-leave status, education and employment status, treatment, care, and support). A composite score may be summarised for ASI, but the rationale for using the ASI questions in the trial is to benefit from the context-specific index developed for the target group within AS.

Quality of life (QoL) outcomes are assessed by the EuroQol 5 Dimension (EQ-5D) [74] and the Manchester Short Assessment of Quality of Life (MANSA) instrument (see below) [75]. The EQ-5D is used to study the effectiveness of perceived QoL dimensions. It comprises 5 health-related quality of life dimensions, mobility, self-care, usual activities, pain/discomfort, and anxiety/depression with three gravity levels (no problem, moderate problem, and extreme problem), and a visual analogue scale on global QoL (1–100) [74]. An economic evaluation is also available, i.e. the scoring of dimensions helps to quantify 243 health states that can be converted to an index utility score and further translated according to country-specific tariffs which value may be considered as the quality-adjusted life-years (QALY). EQ-5D is well known to assess health interventions, also IPS [24].

MANSA is a brief QoL measure developed for persons with mental health problems [75] and has been used in previous IPS research to detect differences between intervention arms [21–23]. MANSA has 12 items on satisfaction with: life as a whole (global well-being), work situation, finances, friends, leisure, living and housing situation, safety, fellow residents, sexual life, family relations, and physical and mental health. Satisfaction is rated on a 7-point scale, with a sum-score range of 12–84. Higher scores indicate better QoL. MANSA has sound psychometric properties and is widely used [75, 76].

WHO-5 Well-being index (WHO-5) is a brief measure of well-being of the last 2 weeks and consists of five positively worded questions to be rated on a 6-point rating scale. The raw score is transformed to a score between 0 and 100 where a higher score indicates worse well-being. The well-being index was developed in 1998 and has been validated as a measurement instrument in a number of studies [77].

To conclude and improve fidelity to the IPS intervention the Supported Employment Fidelity Scale (SEFS) [50] will be used at 6 and 12 months to conclude and detect changes in service delivery, receipt, and fidelity. Data is collected by the process leader (each site) and research administrator the preceding month. Several data sources, e.g. interviews with IPS participants, unit managers, processors, IPS employment specialists and managers, IPS documentation and statistics will form the basis for the review. This standardised procedure of monitoring adherence entails scoring (1 to 5) of 25 items related to staffing, organisation, and services. Higher scores indicate greater adherence to IPS and a higher expectation of vocational outcomes. An external IPS expert will review the gathered data and be in dialogue with the process leader at each site. Adherence to IPS will be shared in project- and operational work groups as well as with a steering group of integrated actors in which context strategies will be developed to target improvements. The TVR intervention will be reviewed in relation to the SEFS scale as well since no available TVR fidelity scale exists. This allows for comparisons between groups regarding similarities and diverse features [20, 22].

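### The stated direction of the WHO-5 score (higher means worse) conflicts with the article's own description of the scale, so the well-being difference could be read with the wrong sign

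*Protocol article*

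**What the plan says.** The WHO-5 is described in the protocol article under Outcomes, Secondary outcome. The construct is well-being: "WHO-5 Well-being index (WHO-5) is a brief measure of well-being of the last 2 weeks". The instrument "consists of five positively worded questions to be rated on a 6-point rating scale". The direction follows: "The raw score is transformed to a score between 0 and 100 where a higher score indicates worse well-being". The article gives no response anchors and no numeric coding, and mentions no reverse scoring. No other section states a different direction for this scale.

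The Objectives section makes well-being a directional secondary hypothesis. Those who benefit from IPS + TAU are expected to "experience better health, quality of life and well-being, and use less care and support in comparison to TVR + TAU participants". The second research question covers the same domain.

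**The concern.** An index of well-being built only from positively worded items would ordinarily be scored so that stronger endorsement gives a higher number and a higher number means better well-being. The article states the opposite without describing the step that would make it true. This is a stated direction that disagrees with the sentence before it, so it is not a detail left to a later document.

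WHO-5 is the only instrument that the article presents specifically as a well-being measure, and well-being belongs to a research question of its own together with health and quality of life. If an analyst or reader takes the printed direction at face value while the items are scored positively, the conclusion on well-being is inverted.

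Blinding makes a clear direction more important. Under Recruitment, allocation, and blinding, the arms stay coded as A and B through analysis and the drawing of conclusions. Which arm did better on this scale must therefore be judged from its documented direction.

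**Working it through.** No power, sample size or alpha calculation depends on this point, and the plan gives no figure to reproduce. The check is one of scoring logic.

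**Inputs from the article (Secondary outcome).** Five items, all positively worded; six response levels; transformed range 0 to 100; stated direction higher = worse.

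**Assumption.** The numeric coding is not given. I take 0 to 5 per item.

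**Step 1, range.** The raw sum runs from 5 × 0 = 0 to 5 × 5 = 25. Multiplying by 4 gives 0 to 100, which matches the stated range. The range alone does not settle the direction, because a fully reversed score, S' = 100 - S, also runs from 0 to 100.

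**Step 2, direction.** If a higher item code means that a positive statement applies more, S = 100 is the best possible well-being. For 100 to be the worst, each item x would have to be recoded as 5 - x. The sum is then 25 - raw, and 4 × (25 - raw) = 100 - S. The printed direction is therefore correct only if all five items are reversed.

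**Step 3, neighbouring scales.** In the same section, higher is better for the Empowerment Scale, POES and MANSA, and higher is worse for HADS, which measures anxiety and depression. In each case the direction follows the construct that the scale is named for. WHO-5 is the exception: it is named for well-being, but its score is said to rise as well-being falls.

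**Step 4, effect on the comparison.** Let d = mean(S, IPS + TAU) - mean(S, TVR + TAU). On the reversed scale the difference is

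(100 - mean IPS) - (100 - mean TVR) = -d.

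Subtracting from a constant leaves the variance unchanged, so the standard error is the same. The test statistic changes sign, the two-sided p-value is unchanged, and a 95% CI of (L, U) becomes (-U, -L). As an illustration only, with a size that is not in the article: under positive scoring d = +10 is a 10-point benefit of IPS + TAU, and under the printed direction the same +10 would be read as a 10-point deterioration.

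The article sets alpha at 5% with 95% CIs and does not state sidedness. The remark on the p-value assumes two-sided tests.

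**The case against.** The strongest reply is that the article does not give the response anchors or the coding. If the trial's coding does run so that high means poor well-being, the printed direction is correct and nothing is reversed. That stands as a limit on the consequence: the text supports saying that the result could be misread, not that it will be. It does not clear the text, because a full reversal of positively worded items would itself have to be stated.

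A second reply is that WHO-5 is one self-reported scale among several secondary measures, that the data can be rescored at any time before reporting, and that Statistical methods promises a more detailed plan before analysis. All of this is true and keeps the point modest. It does not justify leaving a direction in print that conflicts with the description beside it, since the later plan may copy it.

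A reader might also infer that the Empowerment Scale has the same fault. Its responses are described as "ranging from strongly agree [1] to strongly disagree [4", yet "Higher scores represent higher levels of empowerment". The article does not support that reading. With 28 statements coded 1 to 4 the total runs from 28 × 1 = 28 to 28 × 4 = 112, as stated. The codes, range and direction all agree once statements for which agreement is favourable are recoded as 5 - x. The item wording is not given, and subscales on powerlessness and righteous anger leave open that some statements need no recoding. Item-level recoding is also something an article commonly leaves to the full protocol or analysis plan.

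**Conclusion.** The conflict is real and can be seen in two adjacent sentences of the article. Followed as written, with items scored in their positive direction, the stated interpretation would turn the WHO-5 difference from d into -d. Magnitude, standard error and two-sided p-value would not change. The conclusion rests on one assumption, that positively worded items are scored upwards with no undescribed reversal. The documents make this the natural reading but do not confirm it.

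A reader might go further and conclude that an IPS benefit on well-being will be reported as harm, or that the trial's findings as a whole are at risk. Neither follows. The first needs scoring facts that the article does not give. The second is excluded because the primary outcome is register-based employment and nothing in its definition, sample size or analysis uses the WHO-5. This is an error in the description of an instrument that is worth correcting before analysis. It is not a defect on which the trial depends.

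**What to change.** In the WHO-5 paragraph, replace the stated direction with one in which a higher score indicates better well-being, and add the item coding and the transformation to 0 to 100. If the trial really does reverse the score, keep the printed direction and say explicitly that all five items are reverse-coded. Before choosing, check how the item responses are coded in RedCap. Then carry the same direction into the detailed analysis plan and the scoring syntax, so that the sign of the estimate and its interpretation are fixed before the arms are unblinded.

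The cost is a sentence or two of text and one check of the scoring code. No data collection, visit or participant is affected.
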